## Abstract

**Background:**

Delays in starting physical therapy after hospital discharge worsen deconditioning in older adults. Intervening quickly can minimize the negative effects of deconditioning. Telerehabilitation is a strategy that increases access to rehabilitation, improves clinical outcomes, and reduces costs. This paper presents the protocol for a pragmatic clinical trial that aims to determine the effectiveness and cost-effectiveness of a multi-component intervention offered by telerehabilitation for discharged older adults awaiting physical therapy for any specific medical condition.

**Methods:**

This is a pragmatic randomized controlled clinical trial with two groups: telerehabilitation and control. Participants (n=230) will be recruited among individuals discharged from hospitals who are in the public healthcare system physical therapy waiting lists. The telerehabilitation group will receive a smartphone app with a personalized program (based on individual’s functional ability) of resistance, balance, and daily activity training exercises. The intervention will be implemented at the individuals’ homes. This group will be monitored weekly by phone and monthly through a face-to-face meeting until they start physical therapy. The control group will adhere to the public healthcare system’s usual flow and will be monitored weekly by telephone until they start physical therapy. The primary outcome will be a physical function (Timed Up and Go and 30-s Chair Stand Test). The measurements will take place in baseline, start, and discharge of outpatient physical therapy. The economic evaluations will be performed from the perspective of society and the Brazilian public healthcare system.

**Discussion:**

The study will produce evidence on the effectiveness and cost-effectiveness of multi-component telerehabilitation intervention for discharged older adult patients awaiting physical therapy, providing input that can aid the implementation of similar proposals in other patient groups.

**Trial registration:**

Brazilian Registry of Clinical Trials (ReBEC), RBR-9243v7. Registered on 24 August 2020.

**Supplementary Information:**

The online version contains supplementary material available at 10.1186/s13063-021-05387-2.

## Background

Deconditioning causes a significant functional decline in older adults and is often associated with readmissions, institutionalization, and mortality [1–3]. Deconditioning in older adults refers to a systemic physiological change after a period of inactivity and/or immobility [2, 4–6]. These changes may begin during hospitalization, as many older people are confined to bed [7, 8]. Studies demonstrate that deconditioning remains after discharge [9, 10] and the older adults who resume physical therapy immediately after leaving hospital show gains [11, 12]. The literature recommends that deconditioned older adults should receive moderate to high-intensity training focused on resistance exercises, walking, balance, and daily life activities [2].

Older people referred for rehabilitation after discharge may face long waiting lists to start treatment. The imbalance between rehabilitation supply and the growing demand for its service leads to increased waiting time for treatment [13]. This is especially common in low- and middle-income countries such as Brazil [14], whose public healthcare system serves approximately 70% of the population [15]. Specifically in the city of Belo Horizonte, located in the southeastern Brazilian state of Minas Gerais, the delay for starting physical therapy treatment in the public healthcare system can take up to 3 months. Approximately 400 individuals of different ages are waiting for physical therapy; of these, almost 70% are hospital discharges with different types of medical conditions such as postoperative of lower or upper limbs, fractures, and COVID-19. Inactivity during this waiting period may aggravate deconditioning, especially in older adults.

Telerehabilitation may be a viable alternative to reduce the waiting time for physical therapy [16], minimizing the negative impacts of inactivity, such as falls [17], sedentary pattern [18], and loss of strength, mobility, and resistance [19]. Telerehabilitation provides rehabilitation through information and communication technologies such as videoconferencing, telephoning, and smartphone app [20–22]. This rehabilitation modality offers early access to treatment, reduces costs (mostly with transportation), induces the patient to play a more active role in the treatment, and allows the treatment to be adapted to their routine [16, 23–26]. Evidence shows that telerehabilitation is safe [27, 28], effective, and less costly when compared to face-to-face rehabilitation [23, 25, 26]. In patients who underwent orthopedic surgery, telerehabilitation had positive effects on physical function [28, 29], range of motion [30], function, and pain [31]. In addition, the face-to-face and telerehabilitation modalities demonstrated equivalent results for hospital discharged patients [32–37]. More recently, the social isolation resulting from the COVID-19 pandemic has shown that distance healthcare is essential to ensure treatment continuity, especially for older adults [38]. Therefore, investing in programs that reduce costs without compromising the population’s access is essential.

This paper presents the protocol for a pragmatic superiority clinical trial that aims to determine the effectiveness and cost-effectiveness of a personalized exercise program offered by telerehabilitation to minimize the deconditioning of older adults who are, for non-specific conditions, awaiting outpatient physical therapy.

## Methods

### Study design

This is a protocol for a pragmatic randomized controlled clinical trial. Pragmatic trials are used to evaluate the effectiveness of interventions in the actual clinical practice setting. This design maximizes the application and generalization of results by establishing an appropriate basis for decision-making [39, 40]. This study protocol has been reported in accordance with the Standard Protocol Items: Recommendations for Interventional Trials (SPIRIT) Statement [41]. Additional file 1 details the SPIRIT checklist.

### Setting and participants

Participants will be recruited from the waiting list for outpatient physical therapy of the Municipal Health Secretariat of Belo Horizonte, Brazil. All individuals on this list aged ≥ 60 years and referred to physical therapy after hospital discharge will be contacted by telephone for an initial survey to determine whether they fit the inclusion criteria with questions on mobility, cognition, and Internet access. At an in-person meeting, the researchers will detail the study and clarify any questions. The participant will then be asked to sign the consent form and will undergo the initial evaluation. Figure 1 details the study planning.

**Fig. 1 Fig1:**
[figure not shown]
Flow diagram

The inclusion criteria are (1) older adults age ≥ 60 years [42], (2) being on a waiting list for outpatient physical therapy in the public healthcare system for any specific medical condition, (3) have recently been discharged from the hospital, (4) no impediment to unload weight in the lower limbs to perform the telerehabilitation program, (5) walking independently or with the aid of a device and being able to sit and stand up from a chair to perform physical function tests, (6) being in a stable clinical condition to avoid complications during the telerehabilitation program, (7) having a smartphone device with Internet access (their own or a companion’s) for the telerehabilitation intervention, and (8) having a companion during the execution of the exercises at home to ensure the safety of the intervention.

The exclusion criteria are (1) the presence of clinical complications that make physical exercise impossible; 2) neurological disease, such as Parkinson or stroke; (3) a score in the Mini-Mental State Exam less than 13 for people with no schooling, 18 for individuals with low/moderate schooling, and 26 for people with a high level of schooling [43]; and (4) not being able to understand instructions or complete the tests. Excluded individuals will receive a booklet on the importance of staying active while awaiting physical therapy.

### Randomization and allocation

After the initial evaluation, participants will be randomly allocated to the following groups: telerehabilitation (TG) and control (CG). The allocation will be in random blocks sizing four and six, with an allocation rate of 1:1. The randomized sequence will be computer-generated before the start of the study by a researcher not involved in the study and placed in opaque, sealed, sequentially numbered envelopes. This sequence will remain concealed until the participant is allocated to the groups.

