**Fig. 2 Fig2:**
[figure not shown]
Schedule of enrolment, interventions, and assessments (according to SPIRIT)

In the baseline (t0), besides the outcomes, socio-demographic and clinical data will be collected, as well as data on the companion, and information on the use of communication technologies.

In the second evaluation (t1), satisfaction with the intervention and the TG app will also be evaluated. To minimize sample loss, the second evaluation will occur before the start of outpatient physical therapy or up to 1 week after the start of physical therapy treatment. The start of the outpatient physical therapy will be accompanied by weekly phone calls to both groups.

The final evaluation (t2) will take place on the last day of outpatient physical therapy or up to 1 week after discharge. The evaluation will consist of the collection of outcomes and information about outpatient physical therapy. Reasons for program discontinuity and follow-up losses will be recorded throughout the study.

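### All referral conditions share one unstratified randomisation sequence; adjusting for condition would recover precision at almost no cost (minor)

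*Protocol article*

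**What the plan says.** The section Randomization and allocation fixes the scheme: "The allocation will be in random blocks sizing four and six, with an allocation rate of 1:1". It speaks of a single sequence: "The randomized sequence will be computer-generated before the start of the study by a researcher not involved in the study", held in sequentially numbered envelopes. It gives block sizes, ratio, generator and concealment, but no stratification factor.

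The case mix is wide. Setting and participants admits anyone "being on a waiting list for outpatient physical therapy in the public healthcare system for any specific medical condition". The Background says that almost 70% of those waiting are "hospital discharges with different types of medical conditions such as postoperative of lower or upper limbs, fractures, and COVID-19". Two criteria narrow this mix: an exclusion for "neurological disease, such as Parkinson or stroke" and an inclusion requirement of "no impediment to unload weight in the lower limbs to perform the telerehabilitation program". Lower-limb, upper-limb and COVID-19 patients who meet these criteria all remain eligible.

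The primary outcome is physical function by TUG and 30CST. The Data analysis plan names a nonlinear mixed effect model and a between-group test of baseline characteristics. It names no covariate for referral condition and excludes none. Data collection says that at t0 "socio-demographic and clinical data will be collected".

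**The concern.** Walking from a chair and repeated chair stands both load the legs. A patient recovering from lower-limb surgery or a lower-limb fracture may improve on these tests over a wait of up to 3 months without any intervention. A patient referred for an upper limb or after COVID-19 may follow another course. Two such patients can have the same TUG at t0, so the baseline score need not stand in for the condition.

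Blocks of four and six keep the arms equal in number but do nothing to balance condition. If recovery differs by condition and the analysis ignores it, that variation stays in the error term. In any one realised allocation, a surplus of lower-limb patients in one arm also moves the estimate. The sample size gives 80% power with no visible reserve, so either effect could matter to a result near the threshold.

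**Working it through.** **1. The plan's own figure.** Inputs from Sample size: d=0.4, 80% power, alpha 0.05 (taken as two-sided), 15% loss. A two-sample t-test needs 100 per arm, 200 in total. 200 × 1.15 = 230, as stated. (Dividing instead, 200/0.85, gives 236.) After 15% loss, 230 leaves about 196 completers, 98 per arm, with power 0.796.

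**2. Chance imbalance at 115 per arm.** Assume that half the sample is lower-limb orthopaedic.
- SD of the difference in share = sqrt(2 × 0.5 × 0.5/115) = 0.066, or 6.6 points.
- 95% limit = 1.96 × 0.066 = 0.129, or about 13 points.
- Probability of more than 10 points: 0.13.

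For shares of 20% to 50%, the SD is 5.3 to 6.6 points and the 95% limit about 10 to 13 points.

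**3. Shift of an unadjusted difference at that limit.** Assume that natural change differs between condition groups by δ = 0.5 or 1.0 within-condition SD. The planned d is standardised to the total SD, so the shift must be put on that scale: total SD = sqrt(1 + 0.25δ²).

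| δ | Shift, within-condition SD | Total SD | Shift, total SD | Share of d=0.4 |
|---|---|---|---|---|
| 0.5 | 0.065 | 1.031 | 0.063 | 16% |
| 1.0 | 0.129 | 1.118 | 0.115 | 29% |

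Without the rescaling, the upper value would be 0.129/0.4 = 32%, which is too high.

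**4. Variance left in the error.** Share due to condition = 0.25δ²/(1 + 0.25δ²): 5.9% for δ=0.5 and 20% for δ=1.0.

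**5. Average over all randomisations.** This was simulated with 4,000 runs per setting, 196 completers, a 30% share (assumption) and a recovery gap D of 0.5, 0.8 or 1.2 total SD (assumption). The analysis was a plain two-group comparison, not the planned nonlinear model.

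| Scheme | Power at d=0.4, D=0.5 / 0.8 / 1.2 | Type I error |
|---|---|---|
| One sequence, unadjusted | 0.80 / 0.79 / 0.79 | 0.044 / 0.051 / 0.054 |
| One sequence, condition as covariate | 0.82 / 0.85 / 0.91 | 0.045 / 0.049 / 0.054 |
| Stratified, unadjusted | 0.81 / 0.82 / 0.84 | 0.040 / 0.040 / 0.019 |
| Stratified and adjusted | 0.83 / 0.85 / 0.92 | 0.046 / 0.054 / 0.053 |

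Stratifying cuts the SD of imbalance from 6.6 to 0.8 points, but nearly all the gain in power comes from the covariate. Stratifying without it makes the test conservative.

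**6. An unlucky allocation.** With the assumptions of step 5 and imbalance at its 95% limit (12.8 points), the shift is 16%, 26% or 38% of d=0.4. Given that imbalance, unadjusted type I error is 0.065, 0.091 or 0.142. Power is 0.65, 0.55 or 0.38 if the imbalance runs against telerehabilitation.

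**7. What would imitate the whole effect.** Imbalance would have to reach 0.4/D = 80, 50 or 33 points, which is about 12, 7.6 or 5.1 SD.

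**The case against.** A reader might infer that, without stratification, healing can pass for a treatment effect or conceal one, so that the comparison is biased. The documents do not support this. Blocked randomisation without strata is valid, chance imbalance is already part of the standard error, and step 5 shows type I error near 5% and power near the planned 80%. Step 7 shows that no plausible imbalance reproduces d=0.4. The conditional figures in step 6 describe a tail event, not the expected behaviour of the design.

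Three further objections carry weight. First, the article gives no share by condition and no recovery rates. Marked differences in natural course are plausible, not documented. The Background describes a list of about 400 people of different ages, and the weight-bearing, mobility, stability and neurological criteria narrow it. Second, most of the benefit lies in a covariate, and a covariate list may sit in an analysis plan that is not shown, so its absence here is not a fault. Third, simple blocked allocation at 230 participants is an accepted choice in a pragmatic trial.

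These points lower the severity but do not remove the point. Stratification belongs to the allocation design, and the section that reports the other allocation details names none. The one step stated for baseline differences is a significance test with no stated consequence. At the 5% level it would flag only imbalances beyond roughly 13 points, so it is a poor trigger for adjustment.

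**Conclusion.** The point holds as a minor one about precision and robustness. The described allocation ignores a factor that is known beforehand and probably related to both primary tests. The group comparison remains unbiased with its nominal error rate.

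The main figure, a shift of 16% to 29% of d=0.4, applies only at the 95% limit of imbalance. It rests on an assumed 50% share, an assumed recovery gap of 0.5 to 1.0 SD and an unadjusted analysis. If the gap is small, little is lost. If it is large, adjustment raises power from about 0.79 to about 0.91 (D=1.2, 30% share).

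**What to change.** Prespecify referral condition, as recorded at t0, as a fixed term in the group comparison. Use two levels: lower-limb surgery or lower-limb fracture versus all other conditions, with upper-limb fractures in the second level. If t0 is one of the repeated responses in the mixed model, let the term vary with time, because it is the course that is expected to differ. Adjust whatever the baseline tests show, and settle this before any outcome data are seen.

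If recruitment has not started, also generate the blocks of four and six separately within these two strata, with one numbered envelope set per stratum. Keep the stratum in the model, since stratifying alone makes the test conservative. If recruitment has started, the covariate alone secures nearly all of the gain.

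The cost is a model term, one extra envelope set with slightly more handling, and a check that the t0 clinical form records referral condition in these two levels. No extra patients or visits are needed.

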### Telerehabilitation intervention

The TG will receive a multi-component intervention that includes resistance exercises targeting the main muscle groups of the lower and upper limbs, and balance exercises. There are strong recommendations for the use of this type of intervention, showing improvement in clinical outcomes in older adults, such as reducing falls and increasing muscle strength and mobility [2, 17–19, 44, 45]. These exercises are easy to perform, do not require special equipment or accessories, and were designed for execution without professional supervision. In addition, the participant will choose an activity from their daily routine that they have difficulty in performing and hope to improve in the short term. The participants’ choosing an activity is a strategy aimed to stimulate engagement in the intervention and increase of their independence.

The exercise program will be carried out three to five times a week with high intensity, as suggested by Falvey et al. (2015) [2]. The volume will have three series; the number of repetitions will be customized based on Borg’s Modified Perceived Exertion Scale [46], with effort levels ranging from five to seven. The exercises’ difficulty levels and their sublevels of progression are shown in Table 1 and Additional file 2. Each participant may carry out the entire exercise program once a day or intermittently, two or three times a day (Table 1).

**Table 1 Tab1:** Exercise description and progressions

EXERCISE	DESCRIPTION	PROGRESSIONS	
**Multiplanar single leg balance reach**	The participant starts this exercise in the standing position, assume single lower limb support, and move the opposite lower limb forward, to the side and backward as far as possible and maintaining the knee as straight as possible. The participant performs 3 series of 8 to 15 repetitions in each direction.	**Basic level**	1. The participant is only allowed single upper limb support on a wall or a stable surface (e.g. table or chair) for balance. The participant is allowed to touch the floor with the forefoot of the swing limb at the longest reach distance.
			2. Same as basic level 1, but with increased number of repetitions (minimum increase of 2 repetitions in each direction).
			1. Same as basic level 2, but the participant increases swing limb reach distance.
		**Moderate level**	2. Same as basic level 3, but the participant is not allowed upper limb support.
			3. Same as moderate level 1, but with increased number of repetitions (minimum increase of 2 repetitions in each direction).
			4. Same as moderate level 2, but the participant increases swing limb reach distance.
		**Advanced level**	1. Same as moderate level 3, but the participant is not allowed to touch the floor with the forefoot of the swing limb at the longest reach distance in the three directions.
			2. Same as advanced level 1, but with increased number of repetitions (minimum increase of 2 repetitions in each direction).
			3. Same as advanced level 2, but the participant increases swing limb reach distance.
**Squat**	The participant starts this exercise in the standing position with the back supported by wall and then squat. The participant performs 3 series of 8 to 15 repetitions.	**Basic level**	1. The participant perform wall squat with small range of motion (approximately 45º of knee flexion).
			2. Same as basic level 1, but with increased number of repetitions (minimum increase of 2 repetitions in each series).
			3. Same as basic level 2, but with increased range of motion (approximately 90º of knee flexion).
		**Moderate level**	1. The participant squat without back support but is allowed bilateral upper limb support on a wall or a stable surface (e.g. table or chair) for balance. In addition, the participant performs ankle plantarflexion at the end of each squat repetition (i.e. rise up on their toes).
			2. Same as moderate level 1, but with increased number of repetitions (minimum increase of 2 repetitions in each series).
			3. Same as moderate level 2, but the participant is only allowed unilateral upper limb support.
		**Advanced level**	1. The participant squat without back and upper limb support by simulating sitting on a chair with small range of motion (approximately 45º of knee flexion). In addition, the participant performs ankle plantarflexion at the end of each squat repetition (i.e. rise up on their toes).
			2. Same as advanced level 2, but with increased number of repetitions (minimum increase of 2 repetitions in each series).
			3. Same as advanced level 1, but with increased range of motion (approximately 90º of knee flexion).
**Forward lunge**	The participant starts this exercise in the standing position and then perform forward lunge alternating lower limbs. The participant performs 3 series of 8 to 15 repetitions.	**Basic level**	1. The participant performs forward lunge with small range of motion (approximately 45˚ of knee flexion) and is allowed unilateral upper limb support on a wall or a stable surface (e.g. table or chair) for balance.
			2. Same as basic level 1, but with increased number of repetitions (minimum increase of 2 repetitions in each series).
			3. Same as basic level 2, but with increased range of motion (approximately 90º of knee flexion).
		**Moderate level**	1. The participant performs forward lunge with small range of motion (approximately 45˚ of knee flexion) but is not allowed upper limb support.
			2. Same as moderate level 1, but with increased number of repetitions (minimum increase of 2 repetitions in each series).
			3. Same as moderate level 2, but with increased range of motion (approximately 90º of knee flexion).
		**Advanced level**	1. The participant performs forward lunge with small range of motion (approximately 45˚ of knee flexion) and simultaneous trunk rotation to the side of the limb that moves forward. Upper limb support is not allowed.
			2. Same as advanced level 1, but with increased number of repetitions (minimum increase of 2 repetitions in each series).
			3. Same as advanced level 2, but with increased range of motion (approximately 90º of knee flexion).
**Lateral lunge**	The participant starts this exercise in the standing position and then perform lateral lunge alternating lower limbs. The participant performs 3 series of 8 to 15 repetitions.	**Basic level**	1. The participant performs lateral lunge with small range of motion (approximately 30˚ of knee flexion) and is allowed bilateral upper limb support on a wall or a stable surface (e.g. table or chair) for balance.
			2. Same as basic level 1, but with increased number of repetitions (minimum increase of 2 repetitions in each series).
			3. Same as basic level 2, but with increased range of motion (approximately 60º of knee flexion).
		**Moderate level**	1. The participant performs lateral lunge with small range of motion (approximately 30˚ of knee flexion) but is not allowed to use upper limb support for balance.
			2. Same as moderate level 1, but with increased number of repetitions (minimum increase of 2 repetitions in each series).
			3. Same as moderate level 2, but with increased range of motion (approximately 60º of knee flexion).
		**Advanced level**	1. The participant performs lateral lunge with small range of motion (approximately 30˚ of knee flexion) and simultaneous trunk rotation to the side of the limb that moves to the side. Upper limb support is not allowed.
			2. Same as advanced level 1, but with increased number of repetitions (minimum increase of 2 repetitions in each series).
			3. Same as advanced level 2, but with increased range of motion (approximately 60º of knee flexion).
**Wall/kneeling/floor pushup**	The participant starts this exercise in the standing position with feet shoulder-width apart and facing a wall free from any objects or obstacles. The participant is just over one arm’s lengths away from the wall (30 to 45 centimeters). Then, the participant put the palms of both hands flat against the wall at shoulder height, approximately shoulder-width apart, and then lower and lift him/herself against the wall while keeping their feet planted firmly on the floor and maintaining the back and hips straight. The progression to advanced level includes knelling and floor pushup. The participant performs 3 series of 8 to 15 repetitions.	**Basic level**	1. The participant performs bilateral wall pushup with small range of motion (approximately 45˚ of elbow flexion).
			2. Same as basic level 1, but with increased number of repetitions (minimum increase of 2 repetitions in each series).
			3. Same as basic level 2, but with increased range of motion (approximately 90º of elbow flexion).
		**Moderate level**	1. The participant performs unilateral wall pushup with small range of motion (approximately 45˚ of elbow flexion).
			2. Same as moderate level 1, but with increased number of repetitions (minimum increase of 2 repetitions in each series).
			3. Same as moderate level 2, but with increased range of motion (approximately 90º of elbow flexion).
		**Advanced level**	1. The participant performs kneeling pushups with approximately 90˚ of elbow flexion.
			2. Same as advanced level 1, but with increased number of repetitions (minimum increase of 2 repetitions in each series).
			3. The participant performs floor pushups with approximately 90˚ of elbow flexion.

**Additional file 2.** Exercise protocol video.

The exercises will be available in a smartphone app developed for this study. This technology is widely used, being the main form of Internet access [47]. The app will be installed on either the participant’s or the companion’s smartphone. After each exercise, the participants will report their level of pain and difficulty on the app, on a scale of 0 to 5. The exercise program may also be accessed via a computer if the participant prefers this device. After the initial evaluation, participants and their companions will be trained in how to use the app and perform the exercises. Information on deconditioning and the benefits of the proposed exercises will also be provided.

Two previously trained physical therapists who have a master’s degree will be responsible for monitoring the intervention. The proposed exercises and activities will be performed at home, in the presence of a companion to increase the safety of the exercises and facilitate the management of the app. Participants will be monitored by telephone and in-person meetings. The phone calls will take place weekly to monitor the exercise execution, pain, and adverse events. The progression of the exercises’ difficulty through the protocol’s sublevels will be based on this information, as well as those reported daily in the app. The face-to-face meetings will occur monthly (between 24 and 30 days) at the participant’s rehabilitation center. In these meetings, the professionals will evaluate the execution of the exercises and adjust the difficulty level according to the participant’s performance. The intervention will cease when the participant is contacted to begin outpatient physical therapy. Therefore, the participation period in the trial will depend on the waiting time of each participant.

